## Abstract

**Background:**

Over one-third of cancer patients experience clinically significant mental distress, and distress in caregivers can exceed that of the cancer patients for whom they care. There is an urgent need to identify scalable and cost-efficient ways of delivering mental health interventions to cancer patients and their loved ones.

**Objective:**

The aim of this study is to describe the protocol to pilot a mobile app–based mental health intervention in breast cancer patients and caregivers.

**Methods:**

The IntelliCare mental health apps are grounded in evidence-based research in psychology. They have not been examined in cancer populations. This pilot study will adopt a within-subject, pre-post study design to inform a potential phase III randomized controlled trial. A target sample of 50 individuals (with roughly equal numbers of patients and caregivers) at least 18 years of age and fluent in English will be recruited at a US National Cancer Institute designated clinical cancer center. Consent will be obtained in writing and a mobile phone will be provided if needed. Self-report surveys assessing mental health outcomes will be administered at a baseline session and after a 7-week intervention. Before using the apps, participants will receive a 30-min coaching call to explain their purpose and function. A 10-min coaching call 3 weeks later will check on user progress and address questions or barriers to use. Self-report and semistructured interviews with participants at the end of the study period will focus on user experience and suggestions for improving the apps and coaching in future studies.

**Results:**

This study is ongoing, and recruitment will be completed by the end of 2018.

**Conclusions:**

Results from this study will inform how scalable mobile phone-delivered programs can be used to support breast cancer patients and their loved ones.

**Trial Registration:**

ClinicalTrials.gov NCT03488745; https://clinicaltrials.gov/ct2/show/NCT03488745

**International Registered Report Identifier (IRRID):**

DERR1-10.2196/11452

## Introduction

### Background

In the United States, an estimated 266,120 new cases of invasive breast cancer are expected to be diagnosed in 2018 [1]. Breast cancer is the most common form of cancer in women and the second leading cause of cancer-related deaths in women. In the United States, over 40% of newly diagnosed breast cancer patients report clinically significant distress [2]. Cancer affects not only patients but also their caregivers, which can include a partner, relative, or friend. Responsibilities directly (eg, coordinating care) and indirectly (eg, providing emotional support) linked to their loved one’s care leave caregivers at high risk for burnout [3]. However, despite levels of psychological distress that can exceed those of the cancer patients for whom they care [4], caregivers of cancer patients remain an underserved, yet vulnerable, population. Thus, there is an urgent need to identify ways to provide supportive care to both cancer patients and their loved ones.

### Mobile Interventions for Cancer Populations

Although distress screening has become a standard practice for many cancer programs [5], distress intervention through mobile technology remains an important need in the cancer community [6]. Community and health care organizations are important providers of support services for both cancer patients and their caregivers. Many of them are beginning to provide services through virtual means such as the phone and internet. However, existing models of psychosocial intervention that are heavily reliant on human support are costly and not readily scalable to large populations. For example, on-demand phone helplines need to be constantly staffed by nurses or mental health professionals and are limited in their ability to address the needs of a large and growing cancer population in the United States. Given that over 77% of American adults own a mobile phone [7], it is an ideal platform from which to deliver brief, empirically supported interventions to anyone that needs them. Mental health apps are easily scalable and can provide tailored interventions when and where they are most needed.

### Limitations of Prior Work

Despite the promise of mobile phone mental health apps, significant issues need to be addressed before making them widely available to cancer populations. Although researchers are increasingly examining the efficacy and effectiveness of mental health apps, reviews have found that few publicly available apps have any empirical evidence supporting them [8,9]. These reviews generally paint a bleak outlook for the presence of empirically supported mental health apps, which is negatively impacted by the proliferation of mental health apps in recent years. Although more than 10,000 mental health–related apps are available for download, the lack of thorough investigation of these apps by clinical scientists, combined with a lack of government regulatory oversight, makes many of these apps unhelpful at best and dangerous at worst [10-13]. It is, therefore, imperative to empirically validate mental health apps for the population they are intended for, such as mental health apps for cancer populations. Research has found that the majority of apps for cancer either focus on cancer-symptom monitoring or are intended to raise awareness of cancer through fundraising or promoting a charitable organization [6]. A conclusion to be made from these papers is that a dearth of mental health apps have been tested and designed for cancer populations, which served as the impetus for undertaking this study.

Most health-related apps suffer from poor usability for a variety of reasons such as requiring lengthy engagement times that do not match user preferences [14]. In reality, people use apps in short, frequent time bursts and prefer apps that support a single or limited set of tasks [15]. Providing brief and targeted interventions is particularly important for cancer patients and caregivers as the demands of cancer treatment often leave them with small pockets of time throughout the day. Importantly, pairing an app with light coaching can further increase motivation and adherence [16,17]. In contrast to the majority of support apps that do not provide human assistance, light phone coaching can increase adherence by focusing on how apps can address people’s needs and by identifying obstacles to their effective use [16,17].

### Objective of This Study

The purpose of this study is to conduct a pilot study that uses a set of brief, targeted app-delivered interventions that promote mental health. IntelliCare is a collection of apps that use an elemental, skill-based approach to improving mental health [18]. App content is based on evidence-based approaches in cognitive behavioral therapy (CBT) as well as concepts from mindfulness and positive psychology. For example, one of the apps, Thought Challenger (see Figure 1), guides individuals through an exercise to identify and challenge negative thinking styles, a common CBT approach for anxiety and depression. Another app, Purple Chill, provides users with mindfulness audios that can be accessed at any time. Users can download up to 12 publicly available intervention apps, each of which targets a specific aspect of mental health and well-being (eg, identifying maladaptive thoughts, promoting sleep, and increasing relaxation skills). The apps are designed to be interactive and intuitive. Users can complete many exercises (eg, identifying and challenging an unhelpful thought) in less than a minute. Exercises require few instructions to complete and are usually found on the first screen that is presented. Each IntelliCare app has a *help* feature that contains educational and technical content regarding the specific app in question. See Table 1 for a description of IntelliCare apps and their objectives.

IntelliCare apps are available on both Android and iPhone stores. Those from the general public who download the apps are free to use the apps as desired [19]. Similar to prior IntelliCare work [18], participants in this study are instructed to systematically try 1 to 2 apps per week and retain the ones that are most helpful to them. The purpose of this strategy is to gradually expose participants to all of the apps in a systematic manner, until all available apps have been tried. This mirrors face-to-face CBT in which clients are encouraged to acquire various skills through practice. Users will determine which apps to use (see Methods section). In an 8-week study with light phone coaching, over 90% of users with elevated depression and anxiety symptoms used the apps an average of 195 times, for an average length of 1 min [18]. In this initial study, IntelliCare usage was notably higher than what has been observed in other electronic health and mobile health (mHealth) intervention programs. It was also found that using the apps led to large and significant decreases in depression (Cohen *d*=1.4) and anxiety symptoms (Cohen *d*=1.2), as measured by the Patient Health Questionnaire (9-item version [20]) and the Generalized Anxiety Disorder questionnaire (7-item version [21]), respectively [18]. However, the acceptability, usability, and potential impact of IntelliCare apps in *cancer* patients and caregivers are unknown. Cancer patients and caregivers are faced with the multiple physical and emotional sequalae of cancer treatment, making them potentially unique from other populations. To design mental health apps that can benefit cancer populations, it is important to understand their preferences for using them.

The purpose of this trial was to conduct a pilot study to inform a potential phase III randomized controlled trial (RCT). Consistent with prior definitions and reasons for conducting a pilot study [22,23], the goals of this study are to (1) assess the feasibility of various components (eg, recruitment rates, retention rates, and refusal rates) that need to take place in a larger study; (2) understand and identify potential human and data optimization issues (eg, issues of managing the study in a busy clinic and identifying challenges to recruitment from doctors and nurses, whether data show too much or too little variability); and (3) examine whether participants respond to the intervention. Importantly, a pilot study is not only concerned with whether something can be done and how to proceed but includes implementing something in a way intended in part of a future study [22].

**Figure 1 figure1:**
[figure not shown]
Screenshots of the Thought Challenger app as seen on a mobile phone screen.

**Table 1 table1:** Description of IntelliCare apps and their objectives.

App name	Objective
Aspire	Promote awareness of and striving toward personal goals and values. Helps users identify their values and keep track of their progress.
Day to Day	Promote knowledge about ways to bolster mood. Users receive a daily stream of knowledge tidbits and are prompted to build on a theme every day (eg, cultivate gratitude and problem solve).
Daily Feats	Promotes goal setting and attainment. An in-app built calendar allows users to track their successes and identify new tasks to complete.
Worry Knot	Promotes knowledge about worry and provides an interactive exercise to decrease worry. The app also tracks the user’s progress and provides tailored feedback on ways to distract oneself from worrying thoughts.
Social Force	Encourages users to identify supportive individuals in their life. The app prompts users to reach out to these people for encouragement.
My Mantra	Increases self-efficacy and a positive perspective of oneself. The app prompts users to come up with personal mantras and to construct personalized photo albums that serve as reminders of these mantras.
Thought Challenger	Increases the ability to identify and challenge negative thinking patterns. Guides users through a cognitive restructuring exercise and tracks the output of past exercises.
iCope	Promotes coping and positive reinforcement by having users write and send themselves encouraging messages when they are most needed.
Purple Chill	Increases relaxation skills by providing a library of mindfulness and guided meditation audio files.
MoveMe	Promotes mood through physical activity. The app prompts users to schedule exercises throughout the day or week and provides instructional videos and lessons to increase motivation to exercise.
Slumber Time	Promotes healthy sleeping by prompting users to keep an active sleep diary. The app also provides a checklist of things to do before bedtime to promote healthy sleep habits.
Boost Me	Promotes positive mood by having users schedule positive activities throughout the day. A mood tracker allows users to see their progress and the impact of different activities on their mood.

## Methods

### Study Design

This single-group, 7-week, pre- and posttest pilot study will provide IntelliCare apps to a sample of breast cancer patients and their caregivers in the United States. A mixed-methods approach using self-report measures and qualitative interviews will be used to evaluate user satisfaction and potential for adoption in a larger and more diverse cancer population. In addition, because the apps used in this study are not tailored for breast cancer populations, qualitative interviews will yield crucial feedback to determine what changes to the IntelliCare apps can be made in a larger trial. Passively collected app usage data (ie, app launches and app session duration) will inform our understanding of engagement with the apps among cancer patients and caregivers. The decision to use a 7-week duration was based on the duration of brief face-to-face psychotherapy (typically 6-8 weeks) as well as prior reviews of mHealth studies, finding that the duration of app interventions range between 6 days and 8 weeks [8].

### Participants

To limit barriers to entry, inclusion criteria are limited to the following: (1) breast cancer patient or informal caregiver (ie, not receiving compensation for providing care); (2) at least 18 years of age; (3) proficient in English at a sixth grade level; and (4) has a mobile phone or is willing to carry one around if provided. Participants are not required to have a minimum level of familiarity with mobile devices or technology. Participants will be eligible to receive a US $50 gift card for providing user feedback at the end of the study. Study procedures, including the coaching protocol and access to IntelliCare apps, will be identical for both breast cancer patients and caregivers.

A target sample size of 50 (25 patients and 25 caregivers) was chosen, given the exploratory nature of this study. Recruitment of participants will occur in a small breast surgical oncology clinic. Clinics are held on 4 out of 5 weekdays, and the 3 surgical oncologists do not have overlapping clinic times. The recruitment goals were influenced by several factors. First, the patients seen in this clinic are generally early in the breast cancer diagnostic pathway and although it is a time of need for the type of mental health support these apps can provide, it is also a time when it may not be appropriate to recruit them to a study that requires an immediate face-to-face consent and app download process. Second, the logistics of clinic flow, space, and time constraints also influence the pace of recruitment. Overall, 1 to 2 participants per week became the targeted number, which over the course of 29 weeks of active recruitment would yield a sample size between 29 and 58 consented participants.

The primary objective of this study is to inform the feasibility of a larger randomized trial in a clinical setting [22]. Data on usability and user experience from this sample will enable researchers to make iterative changes for future studies. A secondary objective of this study is to provide effect size estimates for a future trial and to pilot the data analyses. This will allow us to explore potential data analytic issues that might arise in a large trial such as missingness and skewness. Within-group analyses will be performed for both breast cancer patients and caregivers (see Data Analysis section). For reference, an effect size of *d=* 1.4 for change in depression and anxiety symptoms was found in a prior noncancer sample [18] at 80% power. However, it may not be appropriate to generalize an effect size from a symptomatic depressed sample to an unselected cancer population. For general reference, the smallest effect size that can be detected with a sample size of 25, using paired *t* tests with 80% power and alpha of .05, is *d*=0.58, whereas the smallest effect sizes that can be detected with a sample size of 35, using paired *t* tests with 80% power and alpha of .05, is *d*=0.49 [24].

### Materials

Participants will use their own personal mobile phone (Android or iPhone). Some individuals may not own a mobile phone or have an appropriate mobile phone plan that enables downloading and using a native mobile phone app. To address these issues, those who do not own a mobile phone or have an incompatible device will be provided with a Samsung S7 Android phone with an unlimited data plan. Those who are provided a phone will be able to use it for nonstudy purposes. A concerted effort was made to include both Android and iPhone users in the study, given the differences between users of these platforms in some prior work [25]. All IntelliCare apps are currently available for Android users, and a subset of iPhone apps are available (as of March 2018), although more are planned for release.

### Recruitment Procedure

Breast cancer patients and their caregivers will be recruited from a breast care clinic. Surgical oncologists will help to identify potential participants, who will be introduced to the study during a normal scheduled visit. Surgical oncologists will offer a study flyer to breast cancer patients and their caregivers during a normal scheduled visit. Patients and caregivers who express an interest in learning about the study will then speak to a research staff member, who will provide more details about the study and answer any questions. If an eligible patient or caregiver expresses interest in participating in the study, he or she will be led through the consenting process by a research staff member. Research staff will describe the aims of the study, introduce the IntelliCare apps, and review the study timeline. Infographics will serve as visual aids to improve understanding of the study components and timeline. Individuals who provide written consent will schedule a 30-min coaching call to take place sometime within the next 10 days. They will also be guided to download the apps but will be told not to open them until the coaching call. Downloading the apps at the end of the consenting process will allow coaching calls to be kept to within the allotted 30-min time frame. Participants will also have the option to download a separate app (ie, not part of the IntelliCare app suite) that passively collects location and movement data from their phone’s sensors. This app, Sensus, was developed by University of Virginia researchers [26] and has been used to collect location and movement data in college student samples [27]. Data collected from this app will be used in exploratory analyses to determine whether it is possible to identify behavioral markers of mood and well-being. For example, in a prior study of college students, it was found that the amount of time spent at home was associated with a higher level of anxiety and that more negative affect was linked to a longer homestay duration [27]. Participants will be asked to spend 10 to 15 min to complete measures that assess depression and anxiety symptoms, physical and social functioning, and subjective well-being. Measures will be completed via the Web using Qualtrics Survey Platform through a desktop or laptop computer. Recruitment will cease if the target enrollment is met or funding expires at the end of 2018. The same research staff members are each responsible for consenting participants, conducting coaching calls, and collecting feedback from participants.

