
### Phone Coaching

A coaching protocol was developed based on the Efficiency Model of behavioral intervention technology support [16] and supportive accountability [17]. A similar coaching protocol has been implemented in a prior study of the IntelliCare apps [18]. The primary aims of coaching are to address usability issues, increase engagement with the apps, promote fit by assessing participants’ needs, promote knowledge acquisition of the skills found in the apps, and encourage implementation of the skills in participants’ lives. In keeping with the prior study of IntelliCare [18], coaches are instructed to focus on app-related issues and to refrain from doing more traditional counseling with participants. An initial 30-min coaching call will focus on orienting participants to downloading and using the apps, setting expectations of the coach’s role, assessing how the apps may meet participants’ needs, and building rapport. Participants will also be told that they can contact coaches at any time with any app-related questions. Participants who contact coaches for crisis management will be connected with a nearby mental health service provider. Any participant inquiries will receive a response within 1 working day. Following the initial coaching call, participants will receive a short message service (SMS) text message (via Qualtrics Survey Platform SMS tool) every week to remind them to download and try 1 to 2 new IntelliCare apps. Coaches have a bachelor’s degree (not in counseling) and are trained and monitored by the lead author (PC), who has a PhD in clinical and community psychology and over 8 years of experience in conducting psychological assessments and psychotherapy. Coaches received a detailed coaching manual and will attend weekly supervision meetings throughout the duration of the study.

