### Measures and Outcomes

#### Primary Objective and Measures

Because a significant barrier to conducting this study is the enrollment of participants in a busy clinical setting, we will consider the study feasible if (1) we are able to recruit 1 to 2 participants per week from a single clinic over 29 weeks; (2) complete follow-up in at least 50% of all recruited subjects; and (3) observe a median app launch rate of around 3.0, as found in prior work [18]. Participants will be asked to provide feedback on the apps and coaching at the end of the study period. The Usability, Satisfaction, and Ease of use (USE [28]) short form scale will be used to examine usability of the IntelliCare apps. It is composed of items that assess user experience (eg, “I would recommend it to a friend,” “It is easy to learn to use it,” and “It is simply to use”). Items are scored on a 7-point Likert scale (1=strong disagree and 7=strongly agree). The USE measure is a validated scale that is commonly used to evaluate user experience of digital interventions. Participants will be asked to describe the most positive and negative aspects of the apps and which apps were most and least helpful and why. If participants stopped using the apps, they will be asked to comment on why and barriers to using the apps.

Participants will also be asked to provide open-ended feedback. Research staff will conduct telephone interviews with participants, which will cover the following topics related to using the apps: general impressions, design quality, technical needs, and design suggestions to promote app implementation and usage. In addition, participants will be asked to provide feedback on the following aspects of phone coaching: general experience with coaches, usefulness of coaching, additional or unmet coaching needs, and suggestions to improve the coaching experience. Thematic analysis will be used to analyze qualitative data gathered from interviews. Data yielded from this mixed-methods approach will be used to make improvements to the apps and phone coaching in future work.

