### Data Analysis

All data will be stored in a secured server for highly sensitive data. Data will be cleaned and analyzed in statistical software packages (ie, SPSS, SAS, and R). Protocol nonadherence will be defined as individuals who fail to complete the baseline and postintervention surveys. Because this pilot study is only being conducted at a single site, a data monitoring committee was not utilized.

Quantitative data on user experience will be analyzed descriptively, to be compared with user data in existing literature. Qualitative user experience data will be reviewed for content and emerging themes through content analysis. Participants’ interview responses will be recorded by research staff. Qualitative responses will be coded and evaluated according to the general domains of (1) ways to improve the design and user interface of the apps; (2) the specific apps that were most helpful (and why); (3) the specific apps that were least helpful (and why); (4) obstacles and barriers to using the apps; and (5) ways to improve the usefulness of coaching calls. Initial coding of the data will be based on a priori domains and will be refined during the analysis process conducted by investigators. Additional themes that are identified will be defined and coded.

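### The plan lets coaches interview their own participants about the coaching, which risks favourable answers and under-reported barriers in that feedback

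*Protocol article*

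**What the plan says.** All references are to the protocol article.

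- **Roles.** Recruitment Procedure ends with: "The same research staff members are each responsible for consenting participants, conducting coaching calls, and collecting feedback from participants".
- **Interviews.** Primary Objective and Measures says: "Research staff will conduct telephone interviews with participants, which will cover the following topics related to using the apps". The same paragraph lists the coaching topics: "general experience with coaches, usefulness of coaching, additional or unmet coaching needs, and suggestions to improve the coaching experience".
- **Status of the feedback.** The same section says: "Participants will be asked to provide feedback on the apps and coaching at the end of the study period". It adds that the mixed-methods data "will be used to make improvements to the apps and phone coaching in future work".
- **Capture.** Data Analysis says that "interview responses will be recorded by research staff" before coding.
- **Relationship.** Phone Coaching gives as aims of the first call orientation to the apps, setting expectations, assessing needs, "and building rapport". It bases the coaching partly on supportive accountability.
- **Self-report.** The Methods paragraph of the Abstract says that self-report as well as semistructured interviews at the end of the study will address user experience and ways to improve the apps and coaching.

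**The concern.** The people whose work is being evaluated also collect the evaluation, by a telephone call that is not anonymous. A participant who found the coaching unhelpful, or who stopped using the apps, may have to say so to the coach who encouraged use. People tend to soften criticism in that position, so the likely result is more praise and fewer barriers or unmet needs.

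These interviews are meant to show what should change before a larger trial. Study Design relies on them to decide how the apps should be altered, and two of the five coding domains in Data Analysis are obstacles to use and ways to make coaching calls more useful. There is no comparison group, so a favourable tilt could not be recognised or corrected afterwards. If coaching problems go unreported, the coaching model is revised less than it should be.

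**Working it through.** The article gives no figure on this point, and its detectable effect sizes concern the paired *t* tests only. The check is therefore a reading of the sections side by side.

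**1. Can a participant be interviewed by their own coach?** Recruitment Procedure gives every staff member all three tasks. Primary Objective and Measures assigns the interviews to research staff without further restriction. Nothing requires the coach and interviewer to differ, and nothing requires them to be the same. The share of interviews done by a participant's own coach could be anything from none to all.

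**2. Is there a safeguard elsewhere?**

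- Phone Coaching describes a scripted manual, role play and weekly supervision, with the manual and role play directed at the coaching calls. No interview procedure is tied to them.
- Data Analysis describes recording and coding, but no independent interviewer and no anonymous collection.
- Limitations covers sample size, the lack of a comparison group, few exclusion criteria, generalisability and phone access. It does not mention the overlap of roles.

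**3. Which data are exposed?**

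| Data | Source | Exposure |
|---|---|---|
| Recruitment of 1 to 2 per week over 29 weeks | Enrolment count | None |
| Follow-up in at least 50% | Completion count | None directly |
| Median app launch rate around 3.0 | Passive usage data | None |
| USE scale | Mode of administration not stated | Low if self-completed |
| Interview feedback on the apps | Telephone, research staff | Some |
| Interview feedback on coaching | Telephone, research staff | Greatest |

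**4. In which direction?** Rapport and accountability to the coach both push towards favourable answers and fewer admitted barriers. The article offers nothing from which to estimate how far. Any numerical shift would have to be assumed, and interview themes have no mean for it to act on.

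**5. Is there still time to change?** Results reports 17 patients and 7 caregivers consented by the end of June 2018: 17 + 7 = 24. Against the target of 50, 50 − 24 = 26 were still to be recruited, which is 26/50 = 52% if the target is met. The intervention lasts 7 weeks (49 days), and 30 June minus 49 days is 12 May. At the end of June, anyone who started after that date also had their end-of-study interview ahead of them. Participants who started earlier may already have been interviewed.

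**The case against.** The case on the other side has several parts.

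- **Own coach.** A reader might infer that each participant is interviewed by the person who coached them. The article does not say so; it says only that each staff member fills all three roles. Who interviews whom may be settled in a fuller protocol or interview guide. This stands, so the point is that the plan allows it. The overlap itself is a stated design choice, not a missing detail, and even a different interviewer would belong to the coaching team.
- **Primary data.** A reader might also infer that the primary data as a whole are biased. That is not supported. Participants gives the primary objective as informing the feasibility of a larger trial, and none of the three feasibility criteria uses interview answers. User feedback does sit under the primary heading, but no threshold or decision to proceed rests on it.
- **Self-report.** Some self-report on apps and coaching appears to exist beside the interviews, going by the Abstract. This stands in part: the article does not say which coaching items it contains, or whether it is completed before the call.
- **Mitigating features.** The questions ask directly for negative aspects, least helpful apps, reasons for stopping and unmet needs. Passive usage data give a check on favourable talk about the apps. Planned coaching is short, at one 30-minute and one 10-minute call. Investigators carry out the analysis in which the coding is refined, and the recording of responses may mean audio, which would leave less room for filtering. These features lessen the risk, but none changes who asks about the coaching, and usage data cannot check opinions of a coach.

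**Conclusion.** The concern holds in a limited form. The plan allows participants to be asked about the coaching by their own coach, with no stated safeguard and no acknowledgement. This is a well-founded risk of favourable answers and under-reported barriers in the interview feedback, greatest for the coaching questions. It is not a demonstrated bias, and its size cannot be computed from the article.

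The conclusion rests on two assumptions: that no rule separating coach from interviewer exists in a document not shown, and that the interviews are the main source of feedback on coaching. If the end-of-study self-report already collects the coaching evaluation privately and before the call, the concern shrinks accordingly. The feasibility conclusion is not threatened. This is a cheap improvement worth making.

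**What to change.** 1. For the remaining interviews, state that no participant is interviewed by the staff member who coached them. The article refers to coaches in the plural, so interviews can be swapped among them. It does not give their number, so confirm that at least two are available.
2. Put the coaching-evaluation items in the self-administered Qualtrics post-survey, to be completed before the interview call. First confirm whether the end-of-study self-report named in the Abstract already does this. This step matters most, because swapping alone still leaves a member of the coaching team asking the questions.
3. Record coach and interviewer IDs for every interview, including those already done where known, so that interviews before and after the change can be told apart.
4. Add the remaining role overlap to Limitations.

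The costs are scheduling effort, an interviewer who knows the participant's history less well, and a change of arrangement part-way through the study, which item 3 makes visible.
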